## Abstract

**Background:**

Prescribing for patients taking multiple medicines (i.e. polypharmacy) is challenging for general practitioners (GPs). Limited evidence suggests that the integration of pharmacists into the general practice team could improve the management of these patients. The aim of this study is to develop and test an intervention involving pharmacists, working within GP practices, to optimise prescribing in Ireland, which has a mixed public and private primary healthcare system.

**Methods:**

This non-randomised pilot study will use a mixed-methods approach. Four general practices will be purposively sampled and recruited. A pharmacist will join the practice team for 6 months. They will participate in the management of repeat prescribing and undertake medication reviews (which will address high-risk prescribing and potentially inappropriate prescribing, deprescribing and cost-effective and generic prescribing) with adult patients. Pharmacists will also provide prescribing advice regarding the use of preferred drugs, undertake clinical audits, join practice team meetings and facilitate practice-based education. Throughout the 6-month intervention period, anonymised practice-level medication (e.g. medication changes) and cost data will be collected. A nested Patient Reported Outcome Measure (PROM) study will be undertaken during months 4 and 5 of the 6-month intervention period to explore the impact of the intervention in older adults (aged ≥ 65 years). For this, a sub-set of 50 patients aged ≥ 65 years with significant polypharmacy (≥ 10 repeat medicines) will be recruited from each practice and invited to a medication review with the pharmacist. PROMs and healthcare utilisation data will be collected using patient questionnaires, and a 6-week follow-up review conducted. Acceptability of the intervention will be explored using pre- and post-intervention semi-structured interviews with key stakeholders. Quantitative and qualitative data analysis will be undertaken and an economic evaluation conducted.

**Discussion:**

This non-randomised pilot study will provide evidence regarding the feasibility and potential effectiveness of general practice-based pharmacists in Ireland and provide data on whether a randomised controlled trial of this intervention is indicated. It will also provide a deeper understanding as to how a pharmacist working as part of the general practice team will affect organisational processes and professional relationships in a mixed public and private primary healthcare system.

## Background

Prescribing in the context of polypharmacy (i.e. multiple medicines) is complicated, as the potential for drug-drug interactions, adverse drug reactions (ADRs) and potentially inappropriate prescribing (PIP) is increased [1]. PIP is defined as the prescribing of medicines where the risk of an adverse event outweighs the clinical benefit or the omission of medicines which are clinically indicated. PIP has been associated with outcomes such as increased hospital admissions [2], accident and emergency (A&E) visits [3], ADRs [4] and healthcare costs [5, 6]. The management of patients with multimorbidity who are taking multiple medicines is challenging, particularly for GPs in primary care, as there is often fragmentation, or poor communication, between primary and secondary care settings [7]. Thus, there has been an increased emphasis on the need to support GPs in the management of these patients [8]. One approach has been the integration of pharmacists into the general practice team. This co-location of pharmacists in general practices has positively affected various areas of chronic disease management and the quality use of medicines [9].

In 2015, the United Kingdom (UK) National Health Service (NHS), a publically funded healthcare system, introduced a pilot practice-based pharmacist initiative in response to a workforce action plan for general practice [10]. To date, studies have shown that pharmacists, working as part of the general practice team, have influenced the safety and quality of prescribing, which has the potential to improve patients’ outcomes [9]. However, there is limited evidence on the impact of a practice-based pharmacist on GP workloads and patient outcomes [11], and it is still unclear whether such interventions are cost-effective, particularly in relation to other approaches to medicines management such as utilisation of electronic prescribing systems and education [8, 12, 13].

Unlike the UK, pharmacists in Ireland have not been integrated into the general practice team. Thus, the feasibility of the integration of pharmacists into Irish general practice teams warrants exploration, prior to evaluation in a full-scale randomised controlled trial (RCT). Before proceeding to a definitive RCT, the intervention will be further refined based on the results of this current study and evolving research literature in this area. The aim of this pilot study is to develop and test an intervention (defined as the general practice pharmacist [GPP] intervention) involving pharmacists working with GPs to optimise prescribing in Ireland, which has a mixed public and private primary healthcare system. The study will determine the costs and potential effectiveness of the GPP intervention and, through engagement with key stakeholders, will explore the potential for an RCT of the GPP intervention in Irish general practice settings.

## Methods

### Study design

This will be a non-randomised pilot study. Pilot studies are used to determine if and how an intervention can be delivered in practice. Pilot studies implement (or part-implement) an intervention on a smaller scale to help researchers decide how to proceed with that intervention in a future, larger study [14]. Non-randomised pilot studies are studies in which all or part of the intervention to be evaluated, and other processes to be undertaken in a future trial, are carried out (piloted) but without randomisation of participants [14]. A qualitative process evaluation and cost of care analysis of the GPP intervention will be conducted. The study will last for 24 months and will be reported using the principles of the Consolidated Standards of Reporting Trials guidelines extension for the reporting of randomised pilot and feasibility studies [15]. The main study intervention period (i.e. the time during which pharmacists will be working within the general practice setting) will last for 6 months. Throughout this time, participating practices will be asked to display a notice informing patients of the study and the role of the pharmacist within the practice team during the intervention period. Should a patient wish to opt-out of the study they can indicate this to the practice staff and subsequently the pharmacist will not access their records. During months 4 and 5 of the 6-month intervention period, a nested Patient Reported Outcome Measures (PROM) study will be undertaken to permit the collection of individual patient data. The nested PROM study was scheduled to take place during months 4 and 5 of the 6-month intervention period as we hypothesised that this would give time for working practices to stabilise and allow pharmacists and the general practice team to familiarise themselves with the implementation of the intervention components at the practice.

### Main study population and recruitment

The study will be conducted in four general practices. Practices eligible for invitation to the study will be identified from the Health Research Board (HRB) Centre for Primary Care Research (CPCR) in Ireland research network. Practices will be eligible to participate if they have ≥ 1000 older patients (aged ≥ 65 years) on their patient panel. This will ensure adequate numbers of patients with significant polypharmacy (defined here as ≥ 10 repeat medicines) and allow the feasibility of the intervention to be tested in the nested PROM study. Practices will be purposively selected to reflect a range of practice sizes and types, from both socioeconomically deprived and affluent areas. Eligible practices will be invited to participate via a letter of invitation sent to the practice by email. The invitation email will include a study information pack which consists of a study information leaflet outlining the steps of the intervention and availability of continuing medical education points for participation in the study, practice profile questionnaire and practice consent form.

### Nested PROM study population and recruitment

Using a tool embedded within the general practice prescribing software, the pharmacist will compile a list of patients with significant polypharmacy (defined as ≥ 10 repeat medicines). A random sample of these patients will be selected by the pharmacist and screened for inclusion in the nested PROM study. Patients will be eligible for inclusion in the nested PROM study if they are aged ≥ 65 years and are able to attend their practice or participate in data collection. Patients will be excluded if they have psychiatric or psychological morbidity or cognitive impairment sufficient to impair the provision of informed consent, if they have a life-limiting illness likely to lead to death or major disability during the study follow-up period, or if they have already had a medication review/interacted with the pharmacist during the study period.

A letter of invitation (printed on practice headed paper) and a patient information pack will be posted to eligible patients. The patient information pack will include a study information leaflet, consent form and questionnaire to explore their perceived level of health. The letter of invitation will invite them to attend an appointment with the pharmacist for a medication review; they will also be asked to bring their completed questionnaire to this appointment. Eligible patients will be invited until a total of 200 patients (50 patients from each practice) are recruited. Written informed consent will be obtained from these patients (by the pharmacist) prior to any data collection, and follow-up questionnaires will be sent to these patients 6 weeks after the pharmacist has left the practice. Figure 1 gives an overview of the flow of patients through the study.

**Fig. 1 Fig1:**
[figure not shown]
Figure showing the flow of patients through the study

### Intervention development

The design and development of the GPP intervention was informed by the initial stages of the Medical Research Council (MRC) Framework for the design and evaluation of complex interventions to improve health [16]. Within this framework, the MRC defines four stages (development, feasibility and piloting, evaluation and implementation) through which complex interventions should be developed and evaluated. This process is described as ‘fluid’ in nature as researchers may move back and forward between stages, depending on process outcomes and emerging evidence.

The MRC recommends that the ‘development’ of complex interventions be systematic using the best available evidence [16]. The GPP intervention builds upon previous and ongoing research in the Health Research Board (HRB) Centre for Primary Care Research (CPCR) in Ireland, which has focused on PIP and polypharmacy. This includes the OPTI-SCRIPT trial [17], a multifaceted intervention to decrease PIP, and the SPPiRE study [18], the definitive RCT of an adapted version of the OPTI-SCRIPT intervention. Additionally, previous evaluation reports and guidance documents published by the Health Service Executive (HSE) Medicine Management Programme (MMP) have informed the development of this intervention. The HSE is responsible for the management of public health services in Ireland, and the MMP is a multidisciplinary National Clinical Programme with a focus on the safe, effective and cost-effective use of medicines. The MMP aims to provide national leadership on the quality of medicines management, access to medicines and overall expenditure on medicines [19].

### Proposed intervention components

One pharmacist will join the general practice team for a period of 6 months, in accordance with a letter of agreement between them and the practice. The pharmacists will be experienced community-based clinical pharmacists by background and training. The pharmacist will participate in the routine management of practice repeat prescribing (i.e. clinically review repeat prescribing requests made by patients and highlight any issues to the prescriber) and conduct medication reviews (opportunistic and targeted). These medication reviews will focus on high-risk prescribing practices, defined by Guthrie et al. as the prescribing of medication(s) whereby the risk outweighs the benefit [20], PIP as defined by the modified STOPP/START criteria used in the OPTI-SCRIPT trial [17], and SPPiRE study [18], assessment of need for commonly used preventive drugs according to clinical guidelines and the deprescribing of medication(s) that may cause harm or are no longer providing benefit [21]. Pharmacists will also provide prescribing advice and promote recommendations from the MMP relating to cost-effective and generic prescribing [22], as well as promotion of the preferred drug initiative (which promotes the prescribing of a ‘preferred drug’ within an number of specific drug classes) [23]. Additionally, pharmacists will join routine clinical practice meetings and, if appropriate, be available to conduct education sessions based on the specific needs of the practice and support GPs in undertaking clinical audits that can support the GPs’ annual Continuing Professional Development requirements. In the first instance, medication reviews will be chart-based, followed by a patient-facing review as deemed appropriate (this will be determined by the GP). In Ireland, pharmacists cannot prescribe, and therefore, the GP will maintain clinical autonomy throughout the intervention period and all decisions will be verified by the GP prior to any action being taken. Finally, during months 4 and 5 of the study intervention period, pharmacists will recruit 50 patients per practice (total 200 patients) to the nested PROM study. These patients will be invited to a face-to-face medication review with the pharmacist and asked to complete a patient questionnaire to permit the collection of PROMs. Figure 2 provides an overview of the GPP intervention and its components.

**Fig. 2 Fig2:**
[figure not shown]
Overview of the general practice pharmacist intervention and its components

### Comparison group

This will be an uncontrolled pilot study, so there will be no formal comparison group. However, comparison data will be available from the control group of the parallel SPPiRE trial [18], an on-going RCT of a complex intervention to support medicines management for patients ≥ 65 years with multimorbidity in Irish primary care. SPPiRE will also use HSE Primary Care Reimbursement Services data, the national database for pharmacy claims. Data from this national prescribing database will be used as a contemporary national control to compare study practices and non-participating practices and determine if there have been changes in outcomes over the study period at the population-level.

### Outcome measures

As this is a pilot study, a range of medication-related outcome measures will be collected to explore their potential use in an RCT. These outcomes will be collected at practice-level throughout the 6-month intervention period (i.e. main study data) and patient-level during months 4 and 5 of the intervention period (i.e. nested PROM study data). See Table 1 for a summary of the outcomes measured in this study. It provides a comprehensive overview of these outcomes, along with a definition for each outcome collected, and a description of the data source from which the outcome will be recorded.

**Table 1 Tab1:** Summary of the outcomes collected during the General Practice Pharmacist intervention

	Definition	Data Sources & Measurement
Main Study Outcomes (anonymised practice-level data collected throughout six-month intervention)		
Demographics		
Patient age	Age in years	Patient health record
Gender	Male, Female, Other	Patient health record
Patient status	Eligibility for free general practice care	Patient health record
Primary Outcomes		
Patients eligible for review	Number and proportion of patients with polypharmacy presenting for repeat prescriptions per day	Patient health record Pharmacist data collection tool
Medicines reviews	Number of reviews undertaken	Pharmacist data collection tool
Repeat medications	Number and proportion of repeat medications currently prescribed per patient reviewed	Patient health record Pharmacist data collection tool
Polypharmacy	Number and proportion of patients (who request a repeat prescription during the intervention period) with polypharmacy (≥10 repeat medicines)	Patient health record Pharmacist data collection tool
Medicines stopped, started and dose alterations	Number and proportion of medicines stopped, started and altered per patient reviewed	Pharmacist data collection tool
High risk prescribing and potentially inappropriate prescribing	Number and proportion of instances considered to be high risk or potentially inappropriate	Patient health record • High risk prescribing indicators • Modified STOPP/START criteria from OPTI-SCRIPT and SPPiRE
Deprescribing	Number and proportion of episodes of deprescribing per patient reviewed	Pharmacist data collection tool
Generic prescribing	Proportion of generic prescribing per practitioner	Pharmacist data collection tool
Use of Medicines Management Programme preferred drug and prescribing and cost guidance recommendations	Number and proportion of patients with Medicines Management Programme preferred drug per item prescribed per patient reviewed	Pharmacist data collection tool
Adverse drug reactions	Number of adverse drug reactions that caused withdrawal of prescribed medication(s)	Patient health record Pharmacist data collection tool
Inadequate prescription instructions	Number of prescriptions with inadequate instructions (e.g. ‘as directed’)	Patient health record Pharmacist data collection tool
Specific instances of high risk prescribing and potentially inappropriate prescribing	Number and proportion of the following instances: • Long-term use (i.e. >3 months) of non-steroidal anti‐inflammatory drug • Therapeutic duplication • Long terms use (i.e. >3 months) of corticosteroids (e.g. prednisolone) without bisphosphonate	Patient health record Pharmacist data collection tool
Nested PROM Study Outcomes (patient-level data collected during months four and five, pseudo-anonymised until follow-up complete)		
Demographics		
Patient age	Age in years	Self-report Patient health record
Gender	Male, Female, Other	Self-report Patient health record
Marital status	Current marital status at time of baseline questionnaire	Self-report
Ethnicity	Country in which patient was born	Self-report
Education	Highest level of education achieved at time of baseline questionnaire	Self-report
Socioeconomic status	Eligibility for free general practice care and deprivation level of electoral division wherein patient resides and their occupation	Eligibility for free general practice care will be based on self-report and confirmed by patient health record. Deprivation level of electoral division wherein patient resides classified according to Small Area Health Research Unit National Deprivation index. Occupation will be coded with Central Statistics Office occupational categories.
Health related Quality of life [33]	Health related Quality of life five level questionnaire	Self-report
Patients' attitudes towards deprescribing [34]	Patients’ Attitudes Towards Deprescribing questionnaire	Self-report
Treatment burden (unpublished)	Treatment Burden Questionnaire	Self-report
Beliefs about Medicines Questionnaire [35]	Beliefs about Medicines Questionnaire	Self-report
Number of repeat medications	Number of repeat medications currently prescribed	Patient health record
High risk prescribing and potentially inappropriate prescribing	Number and proportion of instances considered to be high risk or potentially inappropriate	Patient health record • High risk prescribing indicators • Modified STOPP/START criteria from OPTI-SCRIPT and SPPiRE
Healthcare utilization		
GP Visits	Number of GP visits	Patient health record
A&E visits	Number of A&E visits	Patient health record Self-report
Hospital admissions (emergency and elective)	Number and rate of admissions Length of stay in days (if admitted) Time to first admission and time to re-admission (days)	Patient health record Self-report
Practice nurse visits	Number of practice nurse visits	Patient health record Self-report
Other primary care visits	Number of visits to other primary care services and identification of those services	Patient health record Self-report
Out-patient department visits	Number of visits to out-patient department services	Patient health records Self-report
Cost Data		
Healthcare utilization	As outlined in the ‘Healthcare utilisation’ section above	Patient health records Self-report
Patient costs	Travel Occupation	Self-report
Staff costs	Costs related to the recruitment and training of the pharmacist Practice-based education of GPs and associated staff also taken into account	Costs per hour (for GP/nurse/secretary input) and per day for pharmacist (use Health Service Executive pay grades for each grade of staff)
Medication costs	Price for drugs supplied through the community drug schemes are listed in the reimbursement files of the Primary Care Reimbursement Service	Primary Care Reimbursement Service reimbursement files
Process Evaluation Data		
Key stakeholder opinions	Stakeholder perspectives	Qualitative interview transcripts

### Sample size

As this is a pilot study, a formal sample size calculation will not be required [24]. The aim is to recruit four practices and, for the nested PROM study, 50 patients per practice. This will be a large enough sample to inform about the practicalities of delivering the intervention, general practice uptake and recruitment and retention of pharmacists.

### Main study data collection and analysis

Throughout the 6-month intervention period, quantitative practice-level data will be collected by the pharmacists using the predefined data collection tool (see Table 1 for more details). These data will be aggregated at the practice-level and will not contain any patient identifiers. Descriptive statistics and estimation using confidence intervals will be the main focus of the analysis. For categorical measures, frequencies and percentages will be presented, and for continuous measures, the mean and standard deviation (SD) will be reported. For continuous measures which show evidence of some skew, a median and interquartile range may also be presented or substituted for the mean and SD.

### Nested PROM study data collection and analysis

When the intervention has been running and processes have been standardised for that practice, PROM data will be collected (following provision of written informed consent). This will be collected during months 4 and 5 of the intervention period in each practice. Eligible patients will be invited to attend a medication review with the pharmacist, and PROM data will be collected using the patient questionnaire (to be completed pre-intervention, i.e. before the medication review with the pharmacist). A follow-up patient postal questionnaire will also be completed. This follow-up questionnaire will be conducted 6 weeks after the medication review with the pharmacist (i.e. post-intervention). Reminders will be sent to any patients who have not completed the follow-up questionnaires; these reminders will be posted 1 month after the follow-up questionnaire has been posted. Demographic and clinical characteristics of patients will be presented using appropriate descriptive statistics (e.g. proportions, means). Differences in outcomes pre- and post-intervention will also be explored. For categorical data, McNemar’s test will be used and a paired-samples *t* test or Wilcoxon signed-rank test (depending on normality of the data) will be used for continuous data. Data analysis will be conducted using Stata and *p* values < 0.05 will be deemed significant.

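### The nested PROM study calls its before-after comparisons exploratory but declares any p < 0.05 significant, across up to 12 unranked outcomes with none named primary

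*Protocol article*

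**What the plan says.** The section on nested PROM data collection and analysis introduces the comparison in exploratory terms: "Differences in outcomes pre- and post-intervention will also be explored". It then names the tests. Paired categorical outcomes get the McNemar test. The remaining outcomes are handled as follows: "a paired-samples *t* test or Wilcoxon signed-rank test (depending on normality of the data) will be used for continuous data". The section closes with one threshold for all of them: p "values < 0.05 will be deemed significant". The outcomes to be tested are not listed there.

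The candidates are in Table 1, under the block headed "Nested PROM Study Outcomes (patient-level data collected during months four and five, pseudo-anonymised until follow-up complete". Setting aside demographics, costs and process evaluation, that block has 12 outcome rows. The sub-heading for primary outcomes appears only in the main-study block of the same table. The nested block has no primary outcome and no order of importance.

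Three other statements set the context:

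- Outcome measures: "a range of medication-related outcome measures will be collected to explore their potential use in an RCT".
- Sample size: "As this is a pilot study, a formal sample size calculation will not be required".
- Main study data collection and analysis: "Descriptive statistics and estimation using confidence intervals will be the main focus of the analysis".

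**The concern.** An exploratory comparison and a fixed significance rule do not fit together. Once the plan says that a p-value below 0.05 counts as significant, each outcome tested is a separate opportunity to report a significant change. With no primary PROM outcome and no ordering, nothing in the article says which result carries weight, so a single isolated p < 0.05 could be presented as an effect of the medication review. The problem comes from the number of outcomes and would remain even if every individual test were exactly valid.

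What is at stake is the reading of the nested study's results. The text under Continuation criteria lists a favourable effect on medicines-related outcomes among the things to be considered before an RCT, and Table 2 has no row that defines it. At least two nested outcomes, the number of repeat medicines and high-risk or potentially inappropriate prescribing, are medicines-related. The p < 0.05 rule is the only rule in the article for declaring that an outcome has changed, so it could be borrowed to satisfy that criterion.

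**Working it through.** There is no calculated figure in the plan to reproduce. The sample size calculation is waived, and 0.05 is the only error rate given.

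**Inputs**

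- Level per test: 0.05, with no adjustment stated (nested PROM analysis section). Sidedness is not stated; two-sided is assumed.
- Number of outcomes, counted from the nested block of Table 1:
  - 4 questionnaires: quality of life, attitudes to deprescribing, treatment burden, beliefs about medicines;
  - 2 prescribing outcomes: number of repeat medicines, high-risk or potentially inappropriate prescribing;
  - 6 healthcare-use outcomes: GP, A&E, hospital admission (counted once), practice nurse, other primary care, out-patient.
  - Total: 4 + 2 + 6 = 12.
- Correlation between test statistics: not given, so a range of 0 to 0.8 is assumed.

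**Formulae**

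With k independent tests and no true change in any outcome, the chance of at least one p < 0.05 is 1 − (1 − 0.05)^k.

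- k = 12: 1 − 0.95^12 = 1 − 0.540 = 0.460.
- k = 4: 1 − 0.95^4 = 1 − 0.8145 = 0.1855.

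The expected number of false positives among 12 tests is 12 × 0.05 = 0.6, whatever the correlation.

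For a common correlation ρ, the test statistics are taken as jointly normal, Z_i = √ρ·C + √(1 − ρ)·E_i, with C and the E_i independent standard normal. The chance is then 1 − P(all |Z_i| ≤ 1.96), obtained by integrating over C.

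| Outcomes tested | ρ = 0 | ρ = 0.3 | ρ = 0.5 | ρ = 0.8 |
|---|---|---|---|---|
| All 12 | 46.0% | 39.7% | 31.9% | 18.6% |
| Four questionnaires | 18.5% | 17.4% | 15.6% | 11.4% |

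Relative to the nominal 5%, the 12-outcome range is 18.6/5 = 3.7 times to 46.0/5 = 9.2 times. For the questionnaires alone it is 11.4/5 = 2.3 times to 18.5/5 = 3.7 times.

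**After the change**

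If a single named outcome is tested and the rest are reported as estimates, the chance of a false-positive significance claim is 5%. If no outcome is tested, no such claim arises.

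**The case against.** The strongest reply is that this is an uncontrolled pilot that says it is exploring outcomes. Family-wise error control is not ordinarily required there, and a pilot need not name a primary PROM outcome. An adjustment or a hierarchy could also sit in an analysis plan that is not shown. All of that stands as far as absence goes: the lack of a multiplicity procedure is not itself the fault. What it does not answer is the rule that the article does state. A threshold that declares results significant is at odds with exploration.

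A second reply is that the main-study section covers aggregated practice-level data and the nested section covers paired patient data, so different methods are no contradiction. That is fair. The main-study approach is therefore cited as a workable model within the same article, and not as proof of inconsistency.

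Three stronger readings are tempting, and the documents do not support them.

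- A reader might infer that at least 12 outcomes will be tested. The article does not say so. The only follow-up that its analysis section describes is a postal questionnaire. Healthcare use also feeds the costing, and the time-to-admission measures do not suit the named paired tests. The number tested could be lower or higher than 12.
- A reader might infer that a false-positive finding is more likely than not. For 12 tests the figure stays below 50% at every correlation considered. Under independence it passes 50% only from 14 tests (1 − 0.95^14 = 51%), and outcomes measured in the same patients are unlikely to be independent.
- A reader might infer that a chance result will decide progression or become the RCT outcome. No Table 2 row uses a PROM p-value: PROM data enter there only as recruitment and retention counts. Nowhere does the article say that RCT outcomes will be chosen by p-value.

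**Conclusion.** The concern holds in a limited form. The article attaches an unadjusted significance rule to comparisons that it describes as exploratory, over a set of up to 12 listed outcomes with no primary and no ordering.

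The size depends on two things that the article does not give: how many of the 12 are tested, and how correlated they are. Testing all 12 inflates the chance of a spurious significant change to somewhere between about 19% and 46%. Testing only the questionnaires puts it at about 11% to 19%. Both ranges are more than twice the nominal 5%. They cover chance error alone and say nothing about time trends or regression to the mean in a design without controls.

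The consequence is confined to how effects are reported and to the undefined continuation criterion on medicines-related outcomes. It does not reach any Table 2 threshold. This should be corrected, but it does not undermine the pilot.

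**What to change.** In the section on nested PROM data collection and analysis:

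1. Delete the sentence part that deems p-values below 0.05 significant.
2. State that each before-after change will be reported as an estimate with a 95% confidence interval, as the main-study section already does for its data.
3. State that these contrasts are exploratory and support no claim of effect.
4. If one test is to be kept, name a single PROM outcome for it at 0.05 and leave the others as estimates.

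The cost is wording only, with the same patients and the same data. The small downside is that isolated p < 0.05 results can no longer be presented as significant effects.
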